## Abstract

**Background:**

Acute-on-chronic liver failure (ACLF) represents a rising global healthcare burden, characterised by increasing prevalence among patients with decompensated cirrhosis who have a 28-day transplantation-free mortality of 33.9%. Due to disease complexity and a high prevalence of socio-economic disadvantage, there are deficits in quality of care and adherence to guideline-based treatment in this cohort. Compared to other chronic conditions such as heart failure, those with liver disease have reduced access to integrated ambulatory care services. The LivR Well programme is a multidisciplinary intervention aimed at improving 28-day mortality and reducing 30-day readmission through a home-based, liver optimisation programme implemented in the first 28 days after an admission with either ACLF or hepatic decompensation. Outcomes from our feasibility study suggest that the intervention is safe and acceptable to patients and carers.

**Methods:**

We will recruit adult patients with chronic liver disease from the emergency departments, in-patient admissions, and an ambulatory liver clinic of a multi-site quaternary health service in Melbourne, Australia. A total of 120 patients meeting EF-Clif criteria will be recruited to the ACLF arm, and 320 patients to the hepatic decompensation arm. Participants in each cohort will be randomised to the intervention arm, a 28-day multidisciplinary programme or to standard ambulatory care in a 1:1 ratio. The intervention arm includes access to nursing, pharmacy, physiotherapy, dietetics, social work, and neuropsychiatry clinicians. For the ACLF cohort, the primary outcome is 28-day mortality. For the hepatic decompensation cohort, the primary outcome is 30-day re-admission. Secondary outcomes assess changes in liver disease severity and quality of life. An interim analysis will be performed at 50% recruitment to consider early cessation of the trial if the intervention is superior to the control, as suggested in our feasibility study. A cost-effectiveness analysis will be performed. Patients will be followed up for 12 weeks from randomisation. Three exploratory subgroup analyses will be conducted by (a) source of referral, (b) unplanned hospitalisation, and (c) concurrent COVID-19. The trial has been registered with the Australian New Zealand Clinical Trials Registry.

**Discussion:**

This study implements a multidisciplinary intervention for ACLF patients with proven benefits in other chronic diseases with the addition of novel digital health tools to enable remote patient monitoring during the COVID-19 pandemic. Our feasibility study demonstrates safety and acceptability and suggests clinical improvement in a small sample size. An RCT is required to generate robust outcomes in this frail, high healthcare resource utilisation cohort with high readmission and mortality risk. Interventions such as LivR Well are urgently required but also need to be evaluated to ensure feasibility, replicability, and scalability across different healthcare systems. The implications of this trial include the generalisability of the programme for implementation across regional and urban centres.

**Trial registration:**

Australian New Zealand Clinical Trials Registry (ANZCTR) ACTRN12621001703897. Registered on 13 December 2021.

WHO Trial Registration Data Set. See Appendix 1

**Supplementary Information:**

The online version contains supplementary material available at 10.1186/s13063-022-06679-x.

## Main text

### Background

Acute-on-chronic liver failure (ACLF) is associated with a rising global healthcare burden, underpinned by increasing prevalence among patients with decompensated cirrhosis [1] and 28-day transplantation-free mortality of 33.9% [2]. A retrospective cost analysis of all ACLF unplanned admissions at our health service demonstrated a 30-day readmission of 34.4% and a 71.0% increase in total hospital costs between 2012 and 2018 [3]. There is evidence of increasing multimorbidity [4] in patients with cirrhosis, with an increasing prevalence of complications from comorbid non-alcoholic fatty liver disease and type 2 diabetes mellitus [5]. ACLF is associated with multi-organ failure, which requires a coordinated, multidisciplinary management approach [6]. Additionally, a high prevalence of socioeconomic disadvantage [7] impedes receipt of guideline-based treatments.

Compared to other conditions such as heart failure, those with ACLF have reduced access to integrated ambulatory care services [8] and care is fragmented through under-resourced outpatient clinics. Alcohol abuse is the most prevalent aetiology and independently contributes to the cirrhotic complications of malnutrition and sarcopenia due to inadequate oral intake of energy and protein, altered gastrointestinal absorption and protein/fat metabolism [9]. The combination of financial disadvantage, low health literacy, and active alcohol use creates a maelstrom of difficult-to-treat malnutrition and sarcopenia. The current model of ambulatory care for chronic liver disease is reactive, fragmented and lacks a robust framework for disease management. For new models of care to be adopted into complex healthcare systems, significant upfront costs need to be justified with high-quality evidence [10], which must address obstacles from patient, staff and healthcare system perspectives [11].

LivR Well is a multidisciplinary intervention aimed at reducing mortality and readmission through a home-based, liver optimisation programme. A prospective, single-arm feasibility study was conducted from March to October 2021 and enrolled 32 patients with ACLF (manuscript in progress). Participants received weekly medical review, nursing support, oral nutritional supplementation and consultation by dietetics, physiotherapy, pharmacy, social work and neuropsychiatry. The primary outcome was safety. Secondary outcomes were attrition, disease severity, healthcare utilisation, and patient-reported outcomes. Participants had a baseline median Charlson Co-Morbidity Index of 4 (IQR 3–5.5) and Model for End-Stage Liver Disease (MELD) score of16.5 (IQR 13–20.5). Handgrip strength in 11/23 (48%) met sex-specific sarcopenia criteria. Three patients died at 16, 148, and 197 days from enrolment. The 28-day mortality was 3% and the 30-day readmission rate was 18.75%. Median MELD score improved to 15 at 28 days (*p* = 0.16). The Chronic Liver Disease Questionnaire showed improvement in ‘fatigue’ (*p* = 0.02) and ‘worry’ (*p* = 0.03), at week 6. Patients, carers, and clinicians reported a positive experience in 100% and generated themes of acceptability, health literacy and insight, and autonomy. LivR Well cost $4947 AUD compared to $16,197 AUD for ACLF hospitalisation [3]. These results indicated that LivR Well was safe and acceptable, and likely to reduce both mortality and costs.

The feasibility study used the Asia-Pacific Association for the Study of Liver (APASL) definition of ACLF as an acute hepatic insult manifesting as jaundice (serum bilirubin ≥85mmol/L) and coagulopathy (International Normalized Ratio (INR) ≥1.5) complicated within 4 weeks by ascites and/or encephalopathy [12]. This study protocol for the RCT uses the European Foundation for the Study of Chronic Liver Failure criteria (page 5, Tables 1 and 2) [13], which grades the severity of ACLF using organ failure scores. Although the APASL definition was used due to our Asia-Pacific location, the decision was made to use EF-CLiF criteria to both identify and stratify the patients with the greatest risk of mortality, and to apply a definition most applicable to the Australian population with an alcohol misuse prevalence of 49.5% in cirrhosis [5] compared to greater chronic hepatitis B prevalence in the Asia-Pacific region at 2.8–7.6% [15] vs. 0.5–0.7% in Europe [16]. Consequentially, the patient population identified using EF-CLiF criteria are anticipated to have greater healthcare requirements and mortality but represent only a proportion of those admitted to hospital with decompensated liver disease. This protocol for a randomised controlled trial (RCT) therefore includes two arms to the trial: (a) those with ACLF and (b) those with hepatic decompensation not meeting EF-CLiF criteria. The RCT aims to provide a robust evaluation of the cost-effectiveness and impact on mortality and re-admission rates in each of these two populations compared to standard care.

**Table 1 Tab1:** ACLF Grading using CLIF-C ACLF criteria [13, 14]

ACLF grade	Criteria
**No ACLF**	No organ failure or One organ failure (liver, coagulation, circulatory, respiratory) with serum creatinine <1.5mg/dL and no HE or Single cerebral failure and serum creatinine <1.5mg/dL
**Grade 1**	Single kidney failure or Single liver, coagulation, circulatory, or respiratory failure + serum creatinine 1.5–1.9mg/dL and/or HE I–II or Single cerebral failure (HE III–IV) + serum creatinine 1.5–1.9mg/dL
**Grade 2**	2 organ failures
**Grade 3**	3 or more organ failures

*mg/dL* milligrammes per deciliter, *HE* hepatic encephalopathy

**Table 2 Tab2:** Defining organ/system failure using the CLIF Consortium Organ Failure Score (CLIF-OF) [14]

Organ system	Parameter	Score=1	Score=2	Score=3
**Liver**	Serum bilirubin (mg/dL)	<6	6≤12	>12
**Kidney**	Serum creatinine (mg/dL)	<2	2<3.5	≥3.5 or renal replacement therapy
**Brain**	West-Haven Grade	0	I-II	III-IV
**Coagulation**	INR	<2.0	2.0<2.5	≥2.5
**Circulation**	MAP (mmHg)	≥70	<70	Vasopressors
**Respiratory**	PaO2/FiO2	>300	≤300 and >200	≤200
	OR SpO2/FiO2	>357	>214 and ≤357	≤214

*mg/dL* milligrammes per deciliter, *INR* International Normalized Ratio, *MAP* Mean arterial pressure, mmHg millimetres of mercury, *PaO2* Partial pressure of arterial oxygen, *FiO2* Fraction of inspired oxygen, *SpO2* pulse oximetric saturation

### Methods/design

#### Aims

To evaluate the impact of the programme on 28-day mortality and 30-day re-admissionTo model the cost-effectiveness of LivR Well compared to usual ambulatory careTo examine the differences in outcomes between those with ACLF and those with hepatic decompensation alone

#### Outcomes

##### Primary outcomes

ACLF cohort: 28-day mortalityHepatic decompensation cohort: 30-day re-admission

Secondary outcomesChanges in liver disease severity using Model for End-stage Liver Disease Score and Child-Pugh class assessed at day 28 and week 12 compared to baselineQuality of life using Chronic Liver Disease Questionnaire and EQ-5D at week 6 compared to baselineCost-effectiveness compared to standard care.

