#### Participants and setting

The study context is a multicentre tertiary health service in Melbourne, Australia with recruitment from three tertiary hospital campuses. Monash Health is the second largest healthcare service in Australia managing a catchment population greater than 1.2 million people [19], which includes the largest Culturally and Linguistically Diverse (CALD) community, the significant burden of socioeconomic disadvantage and the highest unemployment rates in the state of Victoria [20]. The 28-day intervention will be delivered through ‘Hospital in the Home’ (HITH), a medically-led ambulatory care programme supported by physical clinics and home visits by the nursing team. HITH is able to deliver many aspects of acute hospital care in the community to otherwise stable patients including diagnosis and management of acute conditions that would typically require bed-based care

Patients will have access to up to three home visits per week by nursing staff and physiotherapists. The patients will attend a hospital-based ambulatory care liver clinic weekly for a medical and nursing review with a dietitian, social work, addiction medicine, and pharmacist consultations as required. Patients will be referred to LivR Well from an outpatient context, the emergency department or the inpatient ward. Patients with any severity of liver disease are eligible unless receiving end-of-life care. There are no cut-offs for the MELD score or Child Turcotte Pugh score.

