#### Screening and randomisation

Patients will be screened against inclusion and exclusion criteria at the time of diagnosis of ACLF or hepatic decompensation. Those who meet the criteria will be enrolled into the study and provided informed consent. These recruited patients will be randomised in a 1:1 ratio to either the LivR Well programme or to complex care liver clinic in the control arm. Participants will be computer randomised and informed of their allocation by the CLD nurse specialist prior to discharge or within 24 hours of obtaining informed consent. Patients from both study arms will be registered on the Virtual Hospital masterlog through the Microsoft Power Apps program. Due to the nature of the intervention, blinding of study participants or clinical staff administering the LivR Well programme will not be possible. However, outcome ascertainment for the primary outcome, as well as the health services utilisation secondary outcomes will be blinded. Furthermore, all data analyses will be undertaken in a blinded manner. The statistician will be blinded to the feasibility study data results and the treatment allocation of the RCT.

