#### Sample size

Sample size calculations were performed for each of the ACLF and hepatic decompensation arms using a 2-sided alpha of 5%, a power of 80%, and an anticipated 20% dropout.

For the ACLF cohort, we used the primary endpoint 28-day mortality, based on published rates of 22–74%, with a rate of 33.9% demonstrated in a study of 1343 hospitalised patients at 29 liver units in 8 European countries [2]. A 75% reduction in mortality in the intervention group generates a mortality rate of 8.5%, a conservative estimate considering our feasibility study of 59 participants resulted in a 3% 28-day mortality rate. We calculate a total sample size of 120 participants or 60 in each arm for the ACLF cohort. For the hepatic decompensation cohort, the sample size calculation is based on the primary endpoint of 30-day re-admission, which is estimated 17–38% [3, 29, 30]. Re-admission rates in our feasibility were 50% lower than anticipated at 18% by 30-days therefore we used an anticipated 17% 30-day re-admission rate in the intervention arm. We calculate a total sample size of 320 or 160 in each arm for the hepatic decompensation cohort. . Sample size calculation was performed using Stata statistical software, version 16.1 for Mac (StataCorp, College Station, TX, USA).

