#### Statistical analyses

The data analysis for the primary composite endpoint of death, referral for liver transplantation or 30-day readmission from the date of hospital discharge will be undertaken on an intention-to-treat basis. A 28-day mortality rate will be calculated from the date of randomisation. For the primary and other binary outcomes, chi-squared tests will be used to compare the intervention and control groups. Survival analyses will also be undertaken, with the generation of Kaplan-Meier curves and Cox regression analyses to derive (adjusted) hazard ratios. For continuous outcomes, t-tests or non-parametric equivalents (e.g., Mann-Whitney tests) will be applied to compare the intervention and comparator groups. A *p* value of 0.05 is considered significant and 95% confidence intervals will be reported for all effect estimates Three exploratory subgroup analyses are planned: (a) comparing groups by the source of referral—conducted to address bias created following randomisation whereby in-patients in the intervention arm may be discharged home earlier due to perceived safety with regular home visits compared to those in the control arm. This subgroup analysis will account for differences between those admitted from in-patient admission compared to the emergency department or the ambulatory liver clinic; (b) comparing groups by re-enrolment to LivR Well after drop out due to unplanned re-admission to hospital. Data from the first enrolment to LivR Well will be included in the primary outcomes on an intention-to-treat basis and (c) patients with COVID-19 at the time of referral. Analyses will be performed using Stata statistical software, version 16.1 for Mac (StataCorp, College Station, TX, USA).

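### One of the two liver-severity measures is change in Child-Pugh class, which discards within-class change that the Child-Pugh score would record (minor, secondary outcome)

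*Protocol article*

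**What the plan says.** The Outcomes section of the Protocol article lists, as a secondary outcome, change in liver disease severity measured by the MELD score and by "Child-Pugh class assessed at day 28 and week 12", against baseline. So the article itself fixes the scale of each measure: a score for MELD, a class for Child-Pugh.

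The numeric Child-Pugh scale is known to the authors. Participants and setting states: "There are no cut-offs for the MELD score or Child Turcotte Pugh score".

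Statistical analyses gives chi-squared tests for binary outcomes. For the rest it says: "For continuous outcomes, t-tests or non-parametric equivalents (e.g., Mann-Whitney tests) will be applied to compare the intervention and comparator groups". No test is assigned to Child-Pugh by name.

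Sample size describes calculations made "using a 2-sided alpha of 5%, a power of 80%, and an anticipated 20% dropout" for the primary endpoints. It states no power, SD or expected change for any Child-Pugh outcome.

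**The concern.** Child-Pugh class is a three-level cut of a points score. Taking the usual cut points (A 5-6, B 7-9, C 10-15, which the article does not print), a patient who goes from 12 to 10 points improves by two points and is recorded as unchanged. A patient who goes from 10 to 9 improves by one point and is recorded as a full class better. A patient already in class C cannot be recorded as worse.

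The first severity assessment comes at the end of a 28-day programme, when changes of a point or so are plausible. A measure that registers such changes only when they cross one of two boundaries is more likely to miss a real effect. What is at stake is the sensitivity of one of two severity measures within a secondary outcome.

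**Working it through.** **1. Inputs from the documents.** Allocation is 1:1, alpha is 5% two-sided and dropout is 20%. The ACLF cohort has 120 patients (60 per arm) and the decompensation cohort 320 (160 per arm). After dropout:

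- ACLF: 60 × 0.8 = 48 per arm.
- Decompensation: 160 × 0.8 = 128 per arm.

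**2. The plan's own ACLF figure.** The article assumes 33.9% against 8.5% 28-day mortality: "We calculate a total sample size of 120 participants or 60 in each arm for the ACLF cohort". The two-proportion formula is n = [1.96√(2p̄q̄) + 0.842√(p₁q₁ + p₂q₂)]² / (p₁ − p₂)².

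- p̄ = 0.212, so 1.96√0.3341 = 1.133 and 0.842√0.3019 = 0.462.
- n = 1.595² / 0.254² = 39.4, that is 40 per arm.
- With the continuity correction, n is 47 per arm, 94 in total. 94 / 0.8 = 117.5, so 118, which agrees with the stated 120 after rounding.

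The 320 is taken as given, because the article states only a range for the control readmission rate.

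**3. Assumptions for Child-Pugh (none are in the documents).** Baseline score is normal with mean m and SD 2. Follow-up has correlation ρ with baseline, and the intervention arm is lowered by the benefit δ. Both values are rounded and limited to 5-15, then classed with the cut points above. The outcome is change from baseline.

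Closed-form anchor for the unrounded score: SD of change = SD√(2(1 − ρ)). With SD 2 and ρ = 0.6 this is 2√0.8 = 1.79. With 128 per arm, SE = 1.79 × √(2/128) = 0.224. For δ = 0.75, power ≈ Φ(0.75/0.224 − 1.96) = Φ(1.39) = 92%. The simulated 89-91% below is slightly lower because of rounding and the limits of the scale.

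**4. Central settings.** SD 2, ρ = 0.6, m from 8.5 to 10.5; t-test on change in score against Mann-Whitney on change in class:

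| Per arm | Benefit (points) | Power, score | Power, class |
|---|---|---|---|
| 128 | 0.5 | 54-59% | 34-42% |
| 128 | 0.75 | 89-91% | 66-75% |
| 128 | 1.0 | 99% | 91-93% |
| 48 | 1.0 | 72-75% | 48-57% |

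Part of that gap is t-test against rank test. With the Mann-Whitney test on both scales, and m from 7.5 to 10.5, the score has more power in every setting, by about 5 to 24 points. Simulation error is one to two points.

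**5. Dependence on the assumptions.** Here δ is set so that the unrounded score has a nominal 80% power. For 128 per arm and ρ = 0.5, δ = 2.8 × 2 × √(2/128) = 0.70. Mann-Whitney on both scales, SD 2, 128 per arm:

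| Baseline mean | ρ | δ | Score | Class | Loss (points) |
|---|---|---|---|---|---|
| 8 | 0.5 | 0.70 | 73.0% | 61.3% | 12 |
| 9 | 0.5 | 0.70 | 76.4% | 62.1% | 14 |
| 10 | 0.5 | 0.70 | 75.8% | 57.2% | 19 |
| 10 | 0.7 | 0.54 | 75.3% | 48.6% | 27 |
| 11 | 0.7 | 0.54 | 73.8% | 39.1% | 35 |

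The loss grows as more patients sit in class C. Over a wider grid (mean 8-10, SD 1.5-2.5, ρ 0.3-0.7, nominal power 30-90%, t-test), the loss on change runs from about 2 to 32 points. If follow-up values are compared instead of change, it runs from about 1 to 17. The direction never reversed.

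**6. Limit of the ACLF figures.** On the plan's own mortality rates, survivors at day 28 would be 60 × (1 − 0.339) = 39.7 in the control arm and 60 × (1 − 0.085) = 54.9 in the intervention arm, before any other loss. The simulation uses 48 in each arm, with loss unrelated to severity, so its results at 48 per arm only illustrate the effect of coarsening.

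**The case against.** The strongest reply is that sensitivity is already provided: the same outcome includes MELD as a score, and class adds a category that clinicians read at a glance. Both points stand. Only one of two measures is coarsened, and class is worth reporting. Neither is a reason to make class the analysed variable when the score can be analysed and the class tabulated.

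A second reply is that every power figure above rests on inputs the documents do not give. That also stands. The direction is robust, the size is not, and no single range can be presented as the trial's loss.

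Three stronger readings are tempting and are not supported:

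- **That the outcome will be cut further to any class improvement and tested by chi-squared.** Statistical analyses does not say so, and the Mann-Whitney test it allows can handle ordered classes. Coding details may properly sit in an analysis plan that is not shown.
- **That class A will be nearly empty, leaving a two-level B/C outcome.** The inclusion criteria admit previous as well as current decompensation, no score cut-off applies, and no class distribution is given.
- **That class brings no benefit at all.** Its clinical readability is a benefit, and the proposed change keeps it.

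Deaths are also a fair challenge. A t-test on change in score cannot include patients who died, whereas ordered categories can place death last. A rank test on the score can do the same, so this bears on the choice of test and does not favour class.

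**Conclusion.** The point holds as a minor efficiency issue. The article fixes Child-Pugh class as one of two severity measures, and analysing the score gave more power in every setting examined. Under SD 2, correlation 0.6, baseline mean 7.5-10.5 and benefit 0.5-1.0 point, the loss from using class is about 5 to 24 percentage points; wider assumptions give roughly 1 to over 30. These are assumed inputs, and the ACLF-cohort figures are illustrative only. Nothing in the document is contradicted. MELD remains as a numeric measure, no power target is stated for this outcome, and the primary endpoints and sample sizes are untouched.

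**What to change.** In the Outcomes section, replace Child-Pugh class with Child-Pugh score (total points) at day 28 and week 12. Compare arms with the continuous-outcome methods already in Statistical analyses. A rank-based test is the more useful of those options here, since it allows deaths to be placed as the worst rank; if that is wanted, say so in advance. Report Child-Pugh class as a descriptive shift table by arm for clinical interpretation.

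The cost is wording only. The points must be totalled to assign the class, so no extra data or visits are needed. As the article gives the trial as open for recruitment, record the change as an amendment made before outcome data are seen by arm.
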